## Abstract

Non-specific low back pain represents 90–95% of all cases of low back pain and it has a prevalence of 18% in the adult population, assuming a great socioeconomic impact. The main objective of this observational case-control study study is to evaluate if there are differences in the simultaneous contraction of the core muscles between nonspecific low back pain and healthy subjects. This study will be carried out in the Physiotherapy department of the University of Alcalá. Eighty-two participants <18 years old, will be recruited, paired with NSLBP (n = 41) and healthy (n = 41). The main outcome will be the onset muscle contraction of lateral abdominal wall (internal oblique, external oblique and transversus abdominis), pelvic floor, lumbar multifidus and respiratory diafragm. The maneuvers that the subjects will perform will be abdominal drawing in maneouver, contralateral arm lift, valsalva, and voluntary pelvic floor contraction in sitting and standing. As a secondary objective, to analyze the amount of contraction of each muscle group and the capacity of the diaphragms to be excreted in both groups of subjects. Finally, to relate pain and disability.

## Introduction

Low back pain (LBP) has been the leading cause of disability since 1990 [1]. In 85–90% of cases, the exact cause of the pain cannot be determined with certainty and patients are classified as Non-Specific Low Back Pain (NSLBP) [1]. Pain has a prevalence of 18% in the adult population, which has a major socioeconomic impact worldwide [2]. In 10% of people suffering from LBP it becomes chronic [1], as it lasts longer than twelve weeks in a year [2]. Acute LBP has been defined by other guidelines as less than 4,6 or 12 weeks duration [2]. The type of work, obesity and unfavorable habits in daily life have also been considered risk factors that increase the likelihood of NSLBP [2]. It has been proposed that maladaptive social and psychological factors (depression, anxiety, catastrophism and low self-efficacy) may play an important role in the persistence of pain [3]. However, the role of musculoskeletal factors remains unclear.

There is no consensus on an exact definition of the core, this term refers to the abdomino-pelvic functional unit that involves not only vertebral segments with their corresponding passive structures that support it or the neural system, but also the four fundamental pillars that conform it: Lumbar multifidus (LM), Lateral Abdominal Wall (LAW), Respiratory Diaphragm (DPH) and pelvic floor (PF) [4, 5]. All this musculature forms a cylinder that works in synergy, producing a crossroads of lumbo-pelvic forces that provide trunk stability, better trunk control, efficient movement, good balance, and coordination, as well as better motor control (postural firmness and alignment). However, although the term core refers to a number of muscle groups, it should be considered a functional rather than an anatomical term [4, 5].

Various methods have been used to assess muscle behavior and/or core morphology with electromyography (EMG) being the ’Gold standard’. Increasingly, the use of RUSI (’Rehabilitative ultrasound imaging’) and real-time ultrasound (RTUS) has become an alternative to Magnetic Resonance Imaging (MRI) as it has been shown to be reliable in comparison with the ’gold standard’ (EMG or MRI) [6]. The use of Motion Mode (M-Mode) in ultrasound (US) has been proven to be a useful tool for assessing muscle contraction in people with NSLBP [4, 7]. Perhaps one of the limitations in performing US studies of the functional unit of the core simultaneously has been the lack of a measurement tool that supports several probes at the same time.

Numerous authors have attempted to explain the causes of NSLBP of musculoskeletal origin related to alterations in movement, muscle activity and/or changes in muscle atrophy in patients with NSLBP compared to asymptomatic participants [8]. These changes appear to be important factors in the evaluation and treatment of patients with LBP [6].

In relation to the definition of core and motor control, it could be understood that not only the morphological situation of the musculature and its contraction in isolation seems to be important, but also the coordination between the muscle groups that conform this functional unit [9]. Therefore, studies that analyze the global muscular behavior of the core and its morphology in a situation of pain in comparison with healthy subjects would give much information about the possible differences existing between both groups of subjects and their possible implication in NSLBP.

In the present protocol, the synergies between the muscle groups of the core that could be involved in NSLBP pain measured with US will be observed as the main objective. It is considered that an alteration in the synergy and in the global behavior of this functional unit may be related to the perpetuation or cause of NSLBP. As a secondary objective, to analyze the amount of contraction of each muscle group and the capacity of the diaphragms to be excreted in both groups of subjects. Finally, to relate pain and disability.

## Materials and methods

### Study design

An observational case-control study is proposed. The study research will be developed according to the Strengthening the Reporting of Observational Studies in Epidemiology (STROBE) [10] and the Guidelines for Reporting Reliability and Agreement Studies (GRRAS) [11]. Data will be collected between December 2021 and February 2023. The study was conducted according to the guidelines of the Declaration of Helsinki and approved by the Institutional Review Board (or Ethics Committee) of Ethical Committee for Research and Animal Experimentation (CEIM) of the University of Alcalá (CEIM/HU/2019/41).

### Participants

Participants will be chronic NSLBP subjects, and asymptomatic, according to the selection criteria and recruited through non-probability convenience sampling. Participants will contact the University of Alcalá, in Madrid. The participant will be provided with the "Adult Research Patient Information Sheet" (S1 Appendix), an informed consent (S2 Appendix), a ’Participant Data Collection Form’ (S3 Appendix) and the Low Back Pain Questionnaire (S4 Appendix) designed by the research team. Once the subject has signed the Informed Consent form and completed the Data collection form and the Low Back Pain Questionnaire, the inclusion and exclusion criteria will be reviewed by a sub-investigator ([name] or [name]). Finally, the participant will be assigned to the case or control group.

### Selection criteria

The inclusion criteria for the chronic NSLBP group will be:

Subjects who suffer from chronic NSLBP according to the criteria defined in the scientific literature [1, 2].Participants aged between 18 and 60 years old [12].To have a history of NSLBP at least twelve weeks in the last year [2]Have scored their pain greater than or equal to 3 points out of 10 on a Visual Analog Scale (VAS) [13, 14].

The control group will be subjects asymptomatic, who have neither acute nor chronic low back pain at the time of the measurement, nor who have suffered it in the last year since the day of the visit.

Surgical intervention, vertebral pathology (fractures, cancer, or infection) inability to be in the position or to perform the selected maneuvers will be the criteria for exclusion from this study. Pregnancy will also be a criterion for exclusion [12].

### Sample size calculation

The sample size calculation has been carried out with the program ‘GPower 3.1.5’ and based on the main inter-subject factor of a mixed 4-by-2 analysis of variance (ANOVA). An effect size of 0.25 was estimated, with a correlation between repeated measurements of 0.50, a power of 80% and a level of 0.05. The resulting sample size was 82 subjects.

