### Outcomes

The primary outcome will be the onset muscular contraction of the four core muscle groups during the Abdominal Drawing in Maneouver (ADIM), Contralateral Arm Lift (CAL), Valsalva maneuver, and voluntary contraction of the PF, in sitting and standing positions:

Onset muscular contraction of the three muscles that conform the Lateral Abdominal Wall (LAW); Transversus abdominis (TrA), Internal oblique (IO), External oblique (EO).Onset muscular contraction of Lumbar Multifidus (LM).Onset excursion of the Diaphragm (DPH).Onset excursion of the Pelvic Floor (PF).

The secondary outcomes are; the percentage of change in muscle thickness in the LM and LAW (IO,EO,TrA) represented as average contraction thickness (cm)–average thickness at rest (cm) / average thickness at rest (cm)*100 [12]; the excursion of the DPH [15] and the excursion of the bladder trough the contraction of the PF muscles [16]. Finally, the degree of disability through the Oswestry disability questionnaire) [17].

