For the analysis of the differences between the groups in the continuous quantitative dependent variables that meet the assumption of normality, a mixed 4-by-2-by-2 covariance analysis (ANCOVA) will be used, with the maneuver (ADIM, CAL, Valsalva, voluntary PF contraction) and the position (sitting, standing) as intra-subject factors, the group (pain, healthy) as an inter-subject factor, and the BMI (Body Mass Index) as a covariant. The association between abdominal muscle thicknesses with gender, age, and BMI was examined using Pearson’s correlation coefficient and multiple regression analysis. Compliance with the assumption of sphericity will be assessed with the Mauchly test and that of equality of covariance matrices with the Box test. The partial eta-square coefficient (p2) will be used as an estimator of the size of the ANCOVA main effects and interactions.

It will be performed the Kruskal-Wallis H test for analyze the differences between independent variables (cases and controls) and the onset muscular contraction, as a qualitative ordinal dependent variable. On the other hand, the t-Student test for independent samples with Bonferroni correction will be used for the analysis of post-hoc pairwise comparisons. Cohen’s d (d = 2t / √g) will be used as estimator of the effect size of the post hoc comparisons [31].

If any continuous quantitative dependent variable does not meet the assumptions for carrying out the ANCOVAs, robust analogous methods will be used that do not require compliance with those assumptions, following the procedures described by Wilcox [31]

All analyses will be carried out with the software R Version 4.1.0 (R Core Team (2021). R: A language and environment for statistical computing. R Foundation for Statistical Computing, Vienna, Austria. URL https://www.R-project.org/). An α level of 0.05 with 95% confidence intervals (CI) will be assumed for all analyses.

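### The 80% power for 82 subjects belongs to a repeated-measures ANOVA group effect, not to the Kruskal-Wallis test named for the primary outcome, onset

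*Protocol article*

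**What the plan says.** All places are in the protocol article.

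- **Sample size calculation.** The calculation is "based on the main inter-subject factor of a mixed 4-by-2 analysis of variance (ANOVA"). Its inputs are "An effect size of 0.25 was estimated", "with a correlation between repeated measurements of 0.50" and "a power of 80% and a level of 0.05". The result: "The resulting sample size was 82 subjects". The Abstract splits this into 41 cases and 41 controls.
- **Outcomes.** "The primary outcome will be the onset muscular contraction of the four core muscle groups", in four maneuvers and two positions. Six onset variables are listed: three lateral abdominal wall muscles, lumbar multifidus, diaphragm and pelvic floor.
- **Procedures.** Each test is done once in each position.
- **Data processing.** The start of movement is found in M-mode and read against a stopwatch shown in the recording software.
- **Statistical analysis, reliability.** ICC, SEM, minimum detectable difference and Bland-Altman limits are planned, with onset named among the measurements.
- **Statistical analysis, group comparison.** A mixed 4-by-2-by-2 ANCOVA with BMI as covariate is reserved for continuous, normally distributed outcomes, with robust analogues where assumptions fail. Onset goes to a Kruskal-Wallis comparison of cases and controls, as "the onset muscular contraction, as a qualitative ordinal dependent variable".

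**The concern.** The calculation and the primary analysis describe different tests. A between-group main effect in a mixed ANOVA gains power by pooling several correlated measurements per subject. A Kruskal-Wallis test of cases against controls has no repeated-measures term. Unless the values are first combined, it uses one value per subject. No power is given for it.

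The article is also inconsistent about what onset is: a timed, continuous quantity where it is measured and its reliability assessed, but an ordinal one where the groups are compared. Whether the sample size fits the primary analysis turns on which description holds.

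At stake is how a null result on the main objective would be read. At the study's own assumed effect, a reader would put the chance of missing a difference at 20%. Under a per-condition reading of the named test it is about 40 to 45%.

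**Working it through.** **Inputs.** From the Sample size calculation: effect size 0.25, correlation rho = 0.50, alpha 0.05, N = 82, and m = 4 repeated measurements from the 4-by-2 layout. From the Abstract: 41 per group. Assumption: 0.25 is Cohen's f, so d = 2f = 0.50 for two equal groups on a single measurement.

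**1. The plan's own figure.** For the between-subject effect, power comes from a noncentral F with 1 and N − 2 degrees of freedom and

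lambda = f² × N × m / (1 + (m − 1) × rho).

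- N = 82, m = 4: lambda = 0.0625 × 82 × 4 / 2.5 = 8.2; power 0.808.
- N = 80, m = 4: lambda = 8.0; power 0.798.

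The smallest even N reaching 80% is 82. The figure reproduces, which supports reading 0.25 as f and shows that the 80% rests on pooling four measurements.

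**2. One value per subject.** With m = 1, lambda = 0.0625 × 82 = 5.125.

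| Test, 41 per group, d = 0.50, alpha 0.05 | Power |
|---|---|
| F or t test | 0.609 |
| Kruskal-Wallis, normal data without ties (efficiency 3/π = 0.955) | 0.589 |
| The same, simulated (8,000 runs) | 0.588 |
| Kruskal-Wallis, 6 ordered levels, simulated | 0.57 |
| Kruskal-Wallis, 4 ordered levels, simulated | 0.54 to 0.55 |

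For 80% power on one value per subject, the t test would need 128 subjects and Kruskal-Wallis about 128 / 0.955, or roughly 135.

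**3. Kruskal-Wallis on a per-subject mean.** Averaging m measurements raises the standardised difference to d / √((1 + (m − 1) × rho) / m).

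- m = 4: 0.50 / √0.625 = 0.632; power about 0.79.
- m = 8: 0.50 / √0.5625 = 0.667; power about 0.83 to 0.84.

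**4. Onset as continuous in a repeated-measures model, N = 82.** The formula of step 1 is used, leaving aside any effect of the BMI covariate. For m = 8, lambda = 0.0625 × 82 × 8 / 4.5 = 9.11.

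| Setting | m = 4 | m = 8 |
|---|---|---|
| rho = 0.50, alpha 0.05 | 0.808 | 0.847 |
| rho = 0.50, alpha 0.05/6 | 0.56 | 0.62 |
| rho = 0.70, alpha 0.05 | 0.72 | 0.74 |

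The alpha of 0.05/6 shows the effect of splitting alpha over the six listed onset variables. The article does not plan this split.

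**The case against.** The best defence is that onset is really continuous. It is timed, and its reliability is assessed with continuous-data methods. If so, the ANCOVA covers it and the power basis largely fits. This stands as a reason for the first remedy below. It does not remove the conflict, because the sentence that assigns onset to a test calls it ordinal.

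Four stronger readings are tempting but not supported:

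- **That the primary test simply has 55 to 60% power.** The article fixes neither the ordinal scale nor the unit of analysis. Kruskal-Wallis can be run on a per-subject summary, with about 79 to 84% power. No such summary is described and averaging suits an ordinal variable poorly, but per-condition testing is not spelled out either.
- **That power falls much further through multiplicity.** Bonferroni is stated only for post-hoc t tests, so a correction across many onset tests would be the reader's own addition.
- **That the 80% covers the continuous secondary outcomes.** The Oswestry score is a secondary outcome completed only by cases, so it has no group comparison. The other secondary outcomes go to a 4-by-2-by-2 ANCOVA with BMI, not to the 4-by-2 ANOVA that was sized.
- **That 82 is an arithmetic error.** It is correct for the test it was computed for.

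It is also fair to note that the sample size section does not name its four-level factor. The four maneuvers are the natural reading, since the ANCOVA has them as its four-level factor, but the article also speaks of four muscle groups.

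**Conclusion.** The point holds as a mismatch between sample size and analysis. The only stated power belongs to a between-group repeated-measures ANOVA of a continuous outcome, while the named primary test is a Kruskal-Wallis test of an ordinal one.

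The size of the shortfall is conditional. It is about 59% against the stated 80%, or about 54 to 55% with four ordered levels. This assumes f = 0.25 carried over as a shift of d = 0.50, one onset value per subject per muscle, maneuver and position, and unadjusted alpha 0.05. The single measurement per maneuver and position makes one value per subject the natural reading, though not a stated rule. It should be settled before analysis, because the power claim for the main objective depends on it.

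**What to change.** State once whether onset is continuous or ordinal, then do one of the following with the same 82 subjects.

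**(a) Treat onset time as continuous.** Analyse it in the repeated-measures model already planned, or its robust analogue, with the group effect as the primary test. Suggested statement: with 82 subjects, d = 0.50 and rho = 0.50, power is about 81% (four conditions) to 85% (eight conditions) per onset variable without multiplicity correction, and about 56 to 62% if alpha is split over the six onset variables. Say that these figures depend on rho; at 0.70 they are 72 to 74% without correction. The authors should confirm that a group effect averaged over conditions answers their question about synergy between muscles.

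**(b) Keep Kruskal-Wallis.** Define the ordinal scale and the unit of analysis. Restate the power for the primary outcome as about 55 to 60% per single-condition test, and say that the 80% refers only to a between-group repeated-measures ANOVA of a continuous outcome.

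The cost is a few sentences in the Sample size calculation and Statistical analysis sections, and under (a) a changed primary model. No further participants or measurements are needed.

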### Outcomes

The primary outcome will be the onset muscular contraction of the four core muscle groups during the Abdominal Drawing in Maneouver (ADIM), Contralateral Arm Lift (CAL), Valsalva maneuver, and voluntary contraction of the PF, in sitting and standing positions:

Onset muscular contraction of the three muscles that conform the Lateral Abdominal Wall (LAW); Transversus abdominis (TrA), Internal oblique (IO), External oblique (EO).Onset muscular contraction of Lumbar Multifidus (LM).Onset excursion of the Diaphragm (DPH).Onset excursion of the Pelvic Floor (PF).

The secondary outcomes are; the percentage of change in muscle thickness in the LM and LAW (IO,EO,TrA) represented as average contraction thickness (cm)–average thickness at rest (cm) / average thickness at rest (cm)*100 [12]; the excursion of the DPH [15] and the excursion of the bladder trough the contraction of the PF muscles [16]. Finally, the degree of disability through the Oswestry disability questionnaire) [17].

### Procedures

The data will be collected by an expert physiotherapist in RUSI with 10 years of experience ([name]) and the principal investigator ([name]) with 60 hours of training in US [18]. Both researchers ([name] and [name]) will be blinded to group assignment during data collection. Two sub-investigators ([name] and [name]) will collect the participant’s Data collection Form and assign him/her to the case or control group. Once the participant has completed all the information and has been assigned to the corresponding group, it will be filed in the investigator file to avoid breaking the blind by principal investigator.

Four wireless US probes, two linear with a 7,5–10 MHz bandwidth and two convex with a 3,5–5 MHz bandwidth will be used. These probes will be held in place by a customized fixation belt manufactured by the research team that has been resulted as a utility model filed with the Spanish patent and trademark office (OEPM; n° 202131486) (Fig 1). The customized fixation belt will allow the simultaneous collection of ultrasound images and videos.

**Fig 1 pone.0285441.g001:**
[figure not shown]
Customized fixation belt.

Three of the probes corresponding to the LAW, LM and DPH will be positioned on the right side of the patient as the sound amplifying window offered by the liver is needed to measure the excursion of the DPH [15]. The fourth probe corresponding to the PF is placed transversely and suprapubically on the subject [16]. The probes placement will correspond to the measurement areas of each muscle group that have been previously validated by different authors [15, 16, 19, 20]. The four US images will be visualized and unified in a computer through a video capture card, where the onset muscle contraction and the morphology of the muscles will be analyzed.

An US analysis will be carried out to evaluate the onset muscle contraction of the four core muscle groups in a global and synergic manner, as well as their individual morphological characteristics during the ADIM, CAL, voluntary PF contraction and Valsalva maneuvers in sitting and standing. The measurements will be taken in these two positions since they have been assumed in as possible risk factors for the appearance of NSLBP and its maintenance [21].

The maneuvers and the positions will be randomized by means of opaque envelopes that will be assigned to each patient to eliminate possible biases. All tests will be performed once in sitting and standing positions. with a 2 minutes break between maneuvers. The authors of this study considered that 2 minutes break between each maneuver and 2 minutes of rest between positions, being low intensity tests, could be enough to avoid participant fatigue. All the maneuvers will be taught before each measurement.

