#### Valsalva maneuver

The Valsalva maneuver is a breathing pattern that consists of forced exhalation with the glottis closed to increase the stability of the spine by increasing the intra-abdominal pressure, since the entire abdominal musculature is activated [25]. The sequence given to the subjects to carry out the Valsalva maneuver will be as follows (1)’’ Take the air into the ears with the mouth and nostrils closed”, (2) ’’apply pressure towards the pelvic floor, as if they intended to defecate’’. No instruction shall be given on the contraction or relaxation of the abdominal muscles or the PF. The muscular activity will be recorded within 3 seconds of the participant’s maximum contraction [25].

The maneuvers and its characteristics are summarized in Table 1.

**Table 1 pone.0285441.t001:** Maneouvers and its characteristics.

Maneuver	Verbal command	Muscle contraction	Rest between maneouvers
**ADIM** [22]	Take a relaxed breath in and out, hold the breath out, and then draw in the lower abdomen without moving their spine”	At the end of the exhalation	2 minutes
**CAL** [23]	Raise the extended arm to shoulder height and hold it for two seconds. Then lower it naturally.	2 seconds	2 minutes
**Voluntary PF contraction** [24]	try to close the urethra as if you wanted to hold back urine"	6 seconds -10 seconds	2 minutes
**Valsalva** [25]	’’apply pressure towards the pelvic floor, as if they intended to defecate’	3 seconds	2 minutes

ADIM, Abdominal Drawing in Maneuver; CAL, Contralateral Arm Lift; PF, Pelvic Floor

The methodology of the US evaluations is summarized in Table 2.

**Table 2 pone.0285441.t002:** Methodology of the ultrasound evaluations.

Muscle	Type of probe	Transducer placement	Transducer bandwidth	Caliper placing
LAW (IO, EO, TrA) [26]	Linear	Right abdominal wall at the midpoint between the lower angle of the thoracic cage and the iliac crest. The medial edge of the transducer shall be placed approximately 10 cm from the alba linear.	7’5MHz	Distance [cm) between the superficial and deep border of each muscle belly, which is marked by the hyperechoic fascial lines. The fascial lines will not be included in the measurement.
LM [27]	Linear	L4-L5 facet joint over the articular pillar and the belly of the L4-L5 muscle over the articular pillar and the belly of the ML muscle.	5MHz	Distance (cm) from the most posterior portion of the zygapophyseal joint of L4-L5 and the muscle surface separating it from the subcutaneous cellular tissue

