PF [24]	Curved	Suprapubic, just in the mid-sagittal and transabdominal plane. The probe will be tilted caudally and posteriorly to obtain a clear image of the postero-inferior aspect (base) of the bladder, which will vary depending on the bladder fullness of the participants.	2MHz-5MHz	Measure the distance (cm) from the base of the bladder to the central part of the convex probe.
DPH [15]	Curved	Right anterior axillary line, Subcostal. The gallbladder and inferior vena cava will be taken as anatomical landmarks.	2’5MHz -3’5MHz	Distance (cm) from the most distal apex of the right hemidiaphragm to the midpoint of the convex probe coinciding with the hyperechogenic curved line of the diaphragm dome.

LAW, Lateral Abdominal Wall; LM, Lumbar Multifidus; PF, Pelvic Floor; DPH, Diaphragm.

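### LM and LAW are recorded on the right in everyone for a reason that applies only to the diaphragm, and pain side is not in the stated analysis; if the difference is specific to the painful side, left-only cases would attenuate the LM and LAW contrasts.

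*Protocol article*

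**What the plan says.** All places are in the Protocol article.

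- **Procedures, text by Fig 1.** "Three of the probes corresponding to the LAW, LM and DPH will be positioned on the right side of the patient", and the reason follows at once: "as the sound amplifying window offered by the liver is needed to measure the excursion of the DPH". No other reason for the side is given. The pelvic floor (PF) probe is suprapubic, so the question does not arise for it.
- **Table 2.** The LAW entry repeats the side ("Right abdominal wall at the midpoint between the lower angle of the thoracic cage and the iliac crest"), as does the DPH entry ("Right anterior axillary line, Subcostal"). The LM entry begins "L4-L5 facet joint over the articular pillar and the belly of the L4-L5 muscle" and names no side, so for LM the right side comes from the Procedures text.
- **Selection criteria.** Cases qualify on a diagnosis of chronic non-specific low back pain, age 18 to 60, duration ("To have a history of NSLBP at least twelve weeks in the last year") and a VAS score of at least 3 out of 10. Side of pain is not mentioned.
- **Outcomes.** The primary outcome is contraction or excursion onset in six structures: TrA, IO, EO, LM, DPH and PF. Thickness change in LM and LAW is a secondary outcome.
- **Statistical analysis.** The ANCOVA has maneuver and position as within-subject factors, with "the group (pain, healthy) as an inter-subject factor, and the BMI (Body Mass Index) as a covariant". Onset is treated as ordinal and compared between cases and controls by Kruskal-Wallis. Pain side appears in neither, nor in Data processing.

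**The concern.** LM and LAW are paired muscles, and one side of each is observed. The stated reason for the side does not carry over to them. Because eligibility does not depend on side, the case group can include people whose pain is only on the left, and their LM and LAW readings then describe the side without pain. The analysis pools them with all other cases at one level of the group factor.

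If the change in onset or thickness lies on the painful side, these readings would look more like control values and pull the group difference towards zero. A null LM or LAW result would then have two readings that the data could not separate: no difference exists, or part of the case group was recorded away from it. LM and LAW account for 4 of the 6 structures in the primary outcome (TrA, IO, EO, LM) and for all the thickness-change outcomes. DPH and PF are not affected.

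**Working it through.** **Inputs from the Protocol article.** Sample size calculation: effect size 0.25 (read as Cohen's f, the G*Power metric), 4 repeated measures, correlation 0.50, alpha 0.05, power 80%, N = 82. Abstract: 41 cases and 41 controls.

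**Inputs not in the documents (assumptions).** q is the share of cases with left-only pain. r is the difference on the non-painful side as a fraction of that on the painful side: r = 0 is wholly side-specific, r = 1 is bilateral.

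**Step 1: reproduce the plan's figure.** For the between-subject effect in a mixed ANOVA with m measures,

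λ = N × f² × m / (1 + (m − 1)ρ), tested on a noncentral F with 1 and N − 2 degrees of freedom.

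λ = 82 × 0.0625 × 4 / 2.5 = 8.20, giving power 80.8%. N = 80 gives 79.8%, so 82 is the smallest even N that reaches 80%. The stated sample size is correct on its own terms and has almost no margin.

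**Step 2: add the dilution.** The mean case-control difference is multiplied by s = 1 − q(1 − r), so f becomes 0.25 × s. The extra variance from mixing two kinds of case is ignored.

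| q | r | s | effective f | λ at N = 82 | power | N for 80% |
|---|---|---|---|---|---|---|
| 0 | any | 1.00 | 0.250 | 8.20 | 81% | 82 |
| 10% | 0 | 0.90 | 0.225 | 6.64 | 72% | 100 |
| 20% | 0 | 0.80 | 0.200 | 5.25 | 62% | 126 |
| 30% | 0 | 0.70 | 0.175 | 4.02 | 51% | 164 |
| 40% | 0 | 0.60 | 0.150 | 2.95 | 40% | 220 |
| 20% | 0.5 | 0.90 | 0.225 | 6.64 | 72% | 100 |
| 30% | 0.5 | 0.85 | 0.2125 | 5.92 | 67% | 112 |
| any | 1 | 1.00 | 0.250 | 8.20 | 81% | 82 |

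The last column shows scale only; no larger sample is proposed.

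**Step 3: what a side-concordant contrast recovers.** Compare only the n₁ cases with right, bilateral or central pain against all 41 controls. With f = 0.25 in two equal groups the difference is 2f = 0.5 SD, so

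λ = (2f)² × n₁ × 41 / (n₁ + 41) × m / (1 + (m − 1)ρ).

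For n₁ = 33 (about 20% left-only): 0.25 × (33 × 41 / 74) × 1.6 = 7.31, power 76%.

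| left-only share (about) | n₁ | λ | power, side-concordant | power, all cases, r = 0 |
|---|---|---|---|---|
| 10% | 37 | 7.78 | 79% | 72% |
| 20% | 33 | 7.31 | 76% | 62% |
| 30% | 29 | 6.79 | 73% | 51% |
| 40% | 25 | 6.21 | 69% | 40% |

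The side-concordant column does not depend on r, because every case in it has pain that includes the recorded side or is central. At r = 0.5 it compares with 72% (q = 20%) and 67% (q = 30%) for all cases, a smaller gain. At r = 1 it compares with 81%, so the contrast then loses a little.

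**Limit of the arithmetic.** These figures belong to the ANOVA in the sample size section. Onset is tested by Kruskal-Wallis, so for the primary outcome they show direction and rough scale, not the power of the stated test.

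**The case against.** The strongest reply is that the harm needs two facts that the documents do not supply: a material share of left-only cases, and a difference tied to the painful side. The Introduction frames the hypothesis as altered synergy and global behaviour of a functional unit, which is not a lateralised hypothesis. For the abdominal wall in particular, nothing in the article leads one to expect change on the side of the back pain. This stands. It makes the loss conditional and is why the range must include zero.

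A second reply is that one fixed side is a reasonable design. There is one probe per muscle group in one belt, cases and controls are treated alike, and choosing the side by pain could reveal group to the blinded examiners. This also stands, although the article does not offer these as its reasons. They argue for leaving the probes where they are and do not explain how pooled LM and LAW results should be read.

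Third, the S4 questionnaire is not shown and may already record side, and an article may leave a sensitivity analysis to a fuller plan. That is fair as to detail. The article does, however, fix the recording side, gives a reason that does not cover two of the three probes, and names its factors and covariate without pain side.

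A reader might infer that the right-side rule biases the group comparison, or that LM and LAW are measured on a wrong side. The documents support neither. A common side can weaken a real difference but cannot create one, and the plan defines no correct side.

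**Conclusion.** The concern holds as a conditional loss of sensitivity and a limit on interpretation. Three facts are plain in the text: right-side recording of LM and LAW, a reason specific to the diaphragm, and no pain-side term in the stated analysis of a case group open to pain on any side.

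The size of the loss rests on assumed q and r. For q of 20% to 30%, power runs from 62% down to 51% if the difference is wholly side-specific and from 72% down to 67% if half of it is on the other side; it stays at 81% if the difference is bilateral. It would go too far to say that the study is underpowered or that dilution will occur, because neither quantity is in the documents and the stated sample size reproduces. The improvement is worth making because it is cheap, and because without it a null LM or LAW result would be hard to interpret.

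**What to change.** Keep the probes, belt and sample size as they are, and make three changes:

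1. Take pain side (right, left, bilateral or central) from the participant-completed S4 Low Back Pain Questionnaire, adding the item if it is absent. The forms go to the sub-investigators, so the examiners stay blinded.
2. In the Statistical analysis, prespecify for the LM and LAW outcomes one sensitivity contrast of cases with right, bilateral or central pain versus controls, reported beside the all-cases comparison. Describe left-only cases but do not test them as a separate level: at 20% there would be about 8 of 41.
3. Word the LM and LAW conclusions as describing right-side behaviour, and say in the Procedures that the liver-window reason applies to the diaphragm.

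Cost: at most one questionnaire item and one extra analysis. The downside is that the sensitivity contrast uses fewer cases and is slightly less precise if the change is bilateral. With 33 cases instead of 41, the standard error rises by a factor of √[(1/33 + 1/41) / (2/41)] = 1.06, about 6%, and power is 76% instead of 81%.
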